## Methods/design

### Design

Controlled, pragmatic, randomized clinical trial with an intervention and control group that will not present differences in any studied characteristics *a priori*.

All medium to large size HCCs from the area will be offered participation and randomly allocated, 7 to the intervention group and other 7 to the control group.

### Studied subjects

The studied population is comprised of all health professionals from 14 primary health care teams of in Area 11 of Madrid who accept to participate (a total of 400 subjects are anticipated to be included).

Inclusion criteria: All health professionals (family physicians, pediatricians, and nurses) who are part of the health care centers (HCC) at the moment of the trial.

### Sample size and sampling

The main outcome variable will be the score on the emotional exhaustion sub-scale of the MBI.

In a previous study performed by this group in the same setting, the average score on this sub-scale was 24, with a standard deviation of 12 points. A change of at least 5 points with respect to the baseline (~20% of the initial value) will be considered significant. These figures do not differ from those found in other populations.

The sample is calculated as non-finite size data, using the formula proposed by Snedecor and Cochran [18].

It is therefore necessary to include ~90 subjects per group, considering a type I error <0.05 and a type II error of 20% (statistical power 80%).

However, we are going to study clusters (health centers) where the variability of the studied parameter will be lower among subjects from the same group and higher among subjects from different groups. This effect, termed the “design effect”, multiplies the needed sample size by a factor ranging from 1.5 to 5. The magnitude of this factor depends on the relationship between the intragroup and intergroup variance, termed the intraclass correlation coefficient [19]. In this case, since there are environmental factors that favor the appearance of burnout, at least moderate intraclass clustering is expected, for which we estimate the design factor will be ~2. Thus, we will need at least 180 subjects per group. If we have a loss to follow-up of ~10%, the studied population will have to be ~200 subjects per group.

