#### Analytical statistics

Initial comparability between the intervention and control groups will be analyzed with the Student's t-test in the case of independent data of quantitative variables (age, years of experience, workload, scores from the questionnaires, etc.) that fit a normal distribution, with the Mann-Whitney U non-parametric test for those not fitting a normal distribution, and with contingency tables in the case of qualitative variables (sex, marital status, professional group, type of contract, etc.).

Univariate correlations between socio-demographic and work characteristics of subjects and their score in the MBI at the beginning of the trial, as well as the correlation between the mentioned characteristics and the change observed during the follow-up, will be analyzed by use of simple linear regression models.

The correlation between the changes associated with burnout syndrome and changes in work-life quality and anxiety, as perceived by health professionals, will be measured using the correlation coefficients for score changes from the MBI, the professional quality of life questionnaire (QPL-35), and Goldberg's GHQ. Pearson's r will be used in the case of normal distributions, and Spearman's rho for non-normal distributions.

Explanatory models will be built to identify work and occupational characteristics related to work satisfaction and burnout. The dependent variable will be the score obtained from the relevant questionnaires at baseline, and the independent variables those considered as relevant in previous theoretical models or proven significant in the univariate analysis.

A comparison of average scores on the MBI will be performed between the intervention and control groups after the intervention and at the end of the follow-up in order to measure the effectiveness of the intervention, and the Student's t-test will be employed for independent data. Confidence intervals of 95% will be calculated for the differences. If the application criteria are not met for that analysis, non-parametric tests will be used (Mann-Whitney U test).

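### With 7 centres per arm, 180 analysed subjects per group give about 73% power on the plan's own inputs, not the stated 80%

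*Protocol article*

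**What the plan says.** The section Sample size and sampling takes its inputs from the group's earlier study, in which "the average score on this sub-scale was 24, with a standard deviation of 12 points". The target is set as follows: "A change of at least 5 points with respect to the baseline (~20% of the initial value) will be considered significant". With a type I error of 5% and a type II error of 20%, the section reaches about 90 subjects per group.

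It then notes that centres are the units of study. It explains that the design effect depends on the ICC, cites a range of 1.5 to 5 for that factor, and chooses its value: "at least moderate intraclass clustering is expected, for which we estimate the design factor will be ~2". From this it concludes: "Thus, we will need at least 180 subjects per group". A 10% loss to follow-up brings the total to about 200 per group.

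The number of randomised units appears only under Design: "7 to the intervention group and other 7 to the control group". Under Randomization the centres are matched in pairs, and one centre of each pair is allocated to each arm.

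**The concern.** A design effect corrects the variance of the treatment difference. It does not correct the degrees of freedom with which that variance is estimated. Multiplying an individually randomised sample size by 2 keeps the large-sample critical value of 1.96, as if the between-centre variance were known or estimated from hundreds of independent units. Here it is estimated from 14 centres.

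The factor of 2 is also not tied to a stated ICC or centre size, so a reader cannot see how sensitive the result is to it. The text expects at least moderate clustering and cites factors up to 5, but picks a value near the low end of that range.

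The interpretation of the result is at stake. A non-significant difference would be read as coming from a trial with 80% power for 5 points, when the real figure is lower even before any less favourable ICC is considered.

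**Working it through.** **Inputs.** From Sample size and sampling: SD 12, difference 5, type I error 0.05, power 80%, design effect 2, 180 analysed per group. From Design: 7 centres per arm. Sidedness is not stated. I take it as two-sided because that reproduces the figure of about 90 (one-sided gives 72) and fits the planned 95% confidence intervals.

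**Reproducing the plan's figures.**
- Before clustering: n = 2 × (1.960 + 0.8416)² × 12² / 5² = 90.4 per group.
- With design effect 2: 2 × 90 = 180.
- With 10% loss: 180 / 0.90 = 200.

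The chain 90, 180, 200 is correct as a large-sample calculation.

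**Power with 180 analysed per group.**
- SE = 12 × √(2 × 2 / 180) = 1.789.
- Noncentrality = 5 / 1.789 = 2.795.
- Normal reference, critical value 1.960: power 79.8%.
- t reference on 2 × (7 − 1) = 12 df, critical value 2.179: noncentral t power **72.8%**. A simulation of centre means (200,000 runs) gave 72.7%.
- Difference detectable with 80% power on 12 df: **5.46 points**.
- If the seven pairs are kept in the analysis (6 df, critical value 2.447) and matching gives no gain in precision: 64.7%.

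**More favourable readings of the same inputs, on 12 df.**
- 182 per group: 73.3%.
- Design effect of 2 applied to the 200 enrolled, so that it is 1.90 at 180 analysed: 75.0%.
- No loss at all, 200 analysed with design effect 2: 77.2%.

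**Implied ICC.** Mean analysed centre size is 180 / 7 = 25.7. Setting 1 + (25.7 − 1) × ICC = 2 gives ICC = 1 / 24.7 = 0.040.

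**Sensitivity on 12 df, 180 per group.** Apart from the implied value of 0.040, the ICC values are assumptions.

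| ICC | Design effect | Power |
|---|---|---|
| 0.02 | 1.49 | 84% |
| 0.040 | 2.00 | 73% |
| 0.05 | 2.24 | 68% |
| 0.07 | 2.73 | 59% |
| 0.10 | 3.47 | 50% |

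Over the cited range of design effects, power is 84% at 1.5, 55% at 3 and 37% at 5.

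**The case against.** The strongest reply is that nothing has been miscalculated. The stated numbers reproduce, and the 80% is written at the step giving 90 per group and only carried over to 180. The 12-df test appears nowhere in the article, which plans a Student's t-test and GEE models with robust standard errors. It is fair that 73% is the power of a test valid for 14 centres, not of the tests as described. This does not rescue the claim. Using 1.96 on centre-level statistics with 14 centres regains 80% power only by raising the type I error to about 7.4%, so the stated error rate and the stated power cannot both hold.

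Second, the factor is given only as approximately 2. A design effect of 1.68 would give 80% on 12 df, and one could call that approximately 2. However, the article used exactly 2 in going from 90 to 180.

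Third, pairing and covariate adjustment could recover the loss. A variance reduction of about 16%, equivalent to a baseline correlation r of about 0.40, would restore 80%. This stands as a possibility, but the sample-size section uses no such correlation and the article gives none. With r as an assumption, baseline adjustment gives 77% at 0.3 and 84% at 0.5.

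The 6-df figure and the powers at ICC 0.05 to 0.10 are conditional and should not be read as the trial's likely power. Whether 0.04 counts as moderate clustering is a matter of judgement, since the article does not define the term. The planned confidence intervals will also show the precision actually achieved, which limits the harm but does not correct the stated power.

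**Conclusion.** The concern holds. With SD 12, a 5-point difference, 180 analysed per group, design effect 2 and 7 centres per arm, power is about 73%, roughly 7 percentage points below the stated 80%. The difference detectable with 80% power is about 5.5 points.

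This rests on a two-sided 5% test that holds its level on 12 between-centre degrees of freedom, equal centre sizes, and no precision gain from matching or baseline adjustment. Unequal centre sizes would lower the figure; useful adjustment or matching would raise it. The shortfall is material but not fatal, and the paragraph should be corrected.

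**What to change.** Rewrite the closing paragraph of Sample size and sampling to:
- state the assumed ICC (about 0.04) and the mean analysed centre size (about 26) behind the design effect of 2;
- compute power with a t reference on the cluster degrees of freedom;
- report about 73% power for 5 points and 80% for about 5.5 points;
- add a short table of power over ICC 0.02 to 0.10.

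If baseline-adjusted emotional exhaustion becomes the primary analysis, give the power under that analysis with the assumed baseline correlation stated (about 84% at r = 0.5).

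The cost is one corrected paragraph and a slightly less favourable stated power. No change to enrolment or to the number of centres is proposed.

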### Intervention

The intervention consists of 16 hours of training, to be held at the subject’s HCC. The workshop involves mixed learning, comprising 4 sessions, each 2 hours long, in addition to personal work previous to and after each session of reading relevant bibliography and performing exercises, self-evaluation, and case studies (8 hours of individual work).

The objective of the intervention is learning from the work experience of professionals attending the workshop to know and recognize the risk and process of the burnout syndrome and the characteristics specific to the health setting, as well as promoting prevention lines by transmitting strategies to manage and control the elements and consequences of the syndrome process (physical, psychological, and social).

Session 1. The burnout syndrome: identifying and coping with the main job stressors.

Session 2. The process of burnout: cognitive and motivational components.

Session 3. Moderating factors of the burnout process: emotional competence and positive personality.

Session 4. Managing the consequences of the burnout: self-care and recovery.

### Randomization

The HCCs that accept to participate will be grouped in pairs based on 3 features: number of professionals, socio-economic area, and urban or rural environment. One center from each pair will be randomly allocated into intervention or control group, and the paired center into the opposite group (allocation by blocks of size 2).

### Measurement tools and included variables

#### Measurement tools

Worker classification regarding burnout syndrome will be performed according to the MBI, which includes 22 items to evaluate emotional exhaustion (EE), depersonalization (DP), and personal fulfillment (PF), with scores ranging from 0 to 6 on the Likert scale. We consider a high degree of burnout in the case of EE ≥ 27 points, DP ≥ 10, and PF <33. Moderate burnout will be considered in the case of 26 < EE < 19 points, 6 < DP < 9 points, and 34 < PF < 39 points. Low levels will be considered for EE ≤ 18 points, DP ≤ 5 points, and PF ≥ 40 points.

Additionally, 2 specific questionnaires for measuring burnout syndrome will be used: the Cuestionario de Desgaste Profesional Médico (CDPM) and the Cuestionario de Desgaste Profesional de Enfermería (CDPE), validated for out setting [3,20].

The CDPE comprises 65 items, with scores ranging from 1 to 4, and evaluates work stressors, professional burnout, resistant personality, and coping.

The CDPM comprises 4 blocks: antecedent variables scale with 24 items, scale of medical burnout syndrome with 12 items, consequent variables scale with 16 items, and scale of positive personal resources with 16 items. Each item is given a value from 1 to 4.

The evaluation of psycho-pathological characteristics of subjects will be carried out using Golberg's GHQ, validated in Spanish by Lobo et al. in 1985 [21]. It consists of 28 items, divided into 4 sub-scales. It is used to estimate the prevalence of psychiatric disease in a specific population and discover cases of psychiatric pathologies in non-specialized consultations. It is not appropriate for performing clinical diagnosis, but can be employed to evaluate symptomatology using its sub-scales: A (somatic symptoms), B (anxiety/insomnia), C (social dysfunction), and D (severe depression). There are 4 possible answers to each question. The Likert scoring system assigns a value from 0 to 3 to each of the 4 possible answers.

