### Data analysis

#### Descriptive statistics

A study on prevalence of “job burnout” in the population will be performed, as well as on their socio-demographic characteristics and work conditions.

Quantitative variables will be described according to their measures of central tendency, mean, and confidence intervals in the case of normal distributions, and by their median and interquartile range in the case of non-normal distributions.

Percentages and confidence intervals will be obtained for qualitative variables.

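### The MBI moderate bands are wrong as written: the EE band is empty, some DP and PF scores fall in no band, and PF = 33 stays unassigned even after the obvious correction

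*Protocol article*

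**What the plan says.** The Measurement tools section makes the MBI the basis for sorting workers: "Worker classification regarding burnout syndrome will be performed according to the MBI". Items are scored "with scores ranging from 0 to 6 on the Likert scale", so subscale totals are whole numbers. It then gives three levels:

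- High: "We consider a high degree of burnout in the case of EE ≥ 27 points, DP ≥ 10, and PF <33".
- Moderate: "26 < EE < 19 points, 6 < DP < 9 points, and 34 < PF < 39 points".
- Low: "Low levels will be considered for EE ≤ 18 points, DP ≤ 5 points, and PF ≥ 40 points".

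The Descriptive statistics section announces a prevalence result: "A study on prevalence of “job burnout” in the population will be performed". It does not say which level, subscale or instrument defines a case.

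The Analytical statistics section plans to correlate MBI change with change in Goldberg's GHQ and in "the professional quality of life questionnaire (QPL-35"). QPL-35 appears nowhere else in the article. The abstract and the Measurement tools section name only the MBI, the CDPM or CDPE, and the 28-item GHQ.

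**The concern.** A three-level rule should place every possible score in exactly one level. This one does not. The moderate EE condition asks for a score above 26 and below 19 at once. The strict inequalities for DP and PF do not meet the adjoining high and low bands. The three conditions in each level are also joined by a conjunction, without saying whether a worker is graded on each subscale separately or must meet all three together.

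At stake is the descriptive grading of workers and any prevalence figure that uses the middle level. These are the only burnout cut-offs in the article. If they are repaired only once scores are known, the choice of where a boundary score goes is open to influence from the results.

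The QPL-35 mismatch is separate and smaller. A change score needs a baseline measurement, so whether the instrument is in the battery has to be settled before the intervention starts.

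**Working it through.** **Inputs.** Bands: Measurement tools. EE mean 24 and SD 12: Sample size and sampling. Expected total of 400: Studied subjects. Two assumptions are not in the article: a roughly normal EE score and, for the second set of figures below, an EE range of 0 to 54.

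**Step 1: whole-number scores tested against the three printed rules, one subscale at a time.**

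| Subscale | Low | Moderate, as printed | High | In no band |
|---|---|---|---|---|
| EE | ≤ 18 | none | ≥ 27 | 19 to 26 |
| DP | ≤ 5 | 7, 8 | ≥ 10 | 6, 9 |
| PF | ≥ 40 | 35 to 38 | < 33 | 33, 34, 39 |

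The eight unassigned EE scores include 24, the mean the plan itself expects.

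**Step 2: share with no EE category if the rule is coded literally.** With a continuity correction,

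P(19 ≤ EE ≤ 26) = Φ((26.5 − 24)/12) − Φ((18.5 − 24)/12) = Φ(0.208) − Φ(−0.458) = 0.259.

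0.259 × 400 ≈ 104 subjects. Restricting the distribution to 0–54 gives 0.266, or about 106 of 400, with 0.311 in the low band and 0.423 in the high band (0.311 + 0.266 + 0.423 = 1.000). Without that restriction, an SD of 10 gives about 31% and an SD of 14 about 22%.

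**Step 3: what each repair achieves.**

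- Reverse the EE signs but keep them strict (19 < EE < 26): 19 and 26 remain unassigned, with probability 0.063 (about 25 of 400), or 0.065 (about 26) on 0–54.
- Make the moderate limits inclusive as well: EE 19–26 and DP 6–9 close completely.
- Make PF inclusive (34–39): PF = 33 is still in no band, because high requires PF below 33 and moderate starts at 34. The article gives no PF distribution, so the share affected cannot be computed.

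**Step 4: does it reach the primary analysis?** The main outcome is the EE score itself, and the group comparison uses mean scores. The sample size uses a 5-point change and SD 12: n = 2 × (1.96 + 0.842)² × 12² / 5² ≈ 90.4, so 91 per group against the stated figure of about 90; 90 × 2 = 180; 180 / 0.9 = 200. These figures reproduce the plan's and use no band.

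**Step 5: joint or separate reading.** Read jointly, a worker with EE 35 and DP 4 is neither high (DP is too low) nor low (EE is too high), and is not moderate either. Read per subscale, the same worker is high on EE and low on DP. The text does not choose between the two.

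**The case against.** The strongest reply is that the EE and DP errors correct themselves. Low and high EE leave exactly 19 to 26 between them, and 19 and 26 are the numbers printed. Low and high DP leave exactly 6 to 9, and 6 and 9 are printed. A competent analyst would use the inclusive bands, so the figure of about 104 to 106 subjects describes literal coding and is not a likely loss. That stands. PF = 33 is what the adjoining bands cannot settle.

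The reply is also right that no effectiveness analysis uses the bands, and that the conjunction can be read simply as a list of cut-offs per subscale. The joint reading is a possibility that the text leaves open, not a demonstrated error.

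Three stronger readings are tempting and go too far:

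- *That the rule cannot classify people.* On EE alone, about 73% (0.311 + 0.423) are placed in the low or high band exactly as printed.
- *That the high and low percentages lack a denominator, or that prevalence cannot be computed.* The percentage high on EE is the number scoring at least 27 divided by everyone assessed, and a faulty middle band changes neither figure. Descriptive statistics does not say that prevalence uses the moderate level.
- *That QPL-35 will not be collected.* The article omits it from its instrument lists but does not call those lists complete, and the full protocol may include it. Nor can one conclude that nothing in the battery measures work satisfaction, since the item content of the CDPM and CDPE is not given. The article shows only that its analysis section and its instrument lists disagree.

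**Conclusion.** The point holds as an error in an operative scoring rule that should be corrected, with limited reach. As printed, the moderate EE band is empty, and EE 19–26, DP 6 and 9, and PF 33, 34 and 39 have no level. Literal coding would leave about 26% of subjects (about 104 to 106 of 400) without an EE category. That rests on an approximately normal EE score with mean 24 and SD 12; the share is about 22% to 31% for SDs of 14 to 10. The enumeration of unassigned scores needs only whole-number totals. After the obvious correction, the one score left unassigned is PF = 33.

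The damage is confined to the three-level grading and to any prevalence figure that uses it. The percentages high or low on a subscale, the primary comparison and the sample size are unaffected. The QPL-35 mismatch is a secondary inconsistency touching one correlation analysis.

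**What to change.** Replace the moderate definitions with contiguous inclusive bands:

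- EE: ≤ 18, 19–26, ≥ 27.
- DP: ≤ 5, 6–9, ≥ 10.
- PF: ≥ 40 for low burnout, then either 33–39 moderate with < 33 high, or 34–39 moderate with ≤ 33 high. The sponsor should state which, according to the scoring it adopts.

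Add one sentence saying whether levels are assigned per subscale or jointly (and, if jointly, how discordant subscales are handled), and one naming the category that counts as a case in the prevalence study. Settle both before scores are classified.

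For QPL-35, either list it among the instruments at baseline and follow-up if it is administered, or delete its correlation analysis.

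The band changes cost wording only. The QPL-35 change costs a line of text if the questionnaire is already in the battery; otherwise it costs one more questionnaire or one secondary analysis.

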### Studied variables

#### Independent variable

Group intervention consisting of 16 hours of training, to be held at the health professional’s own HCC.

#### Dependent variable

Possible burnout condition as identified by score modification, or change, before and after the intervention on the EE scale of the MBI for each subject and for the whole sample.

#### Control variables

● Demographic: age, sex, marital status, number of children, and years of cohabitation with couple.

● Professional category: family doctor, pediatrician, or nurse.

● Years of experience in primary care.

● Type of contract: interim or permanent.

● Performance of tasks involving responsibility (coordination, group leader, supervisor).

● Average practitioner workload per working day.

● Working in shifts.

● Work leave >1 month in the last 6 months.

● General health condition, measured with Goldberg's GHQ-28.

